## Abstract

**Background:**

Previous studies have demonstrated that ICU (intensive care unit) survivors have decreased long-term survival rates compared to the general population. However, knowledge about how to identify ICU survivors with higher risk of death and the adjustable factors associated with mortality is still lacking.

**Methods and Design:**

The FROG-ICU (the French and European Outcome Registry in Intensive Care Units) study is a prospective, observational, multicenter cohort study where ICU survivors are followed up to one year after ICU discharge. Beside one year survival, the study is designed to assess incidence and identifying risk factors for mortality over the year following discharge from the ICU. All consecutive patients admitted in ICU to the 28 participating centers during the study period will be included. Every subject will undergo an evaluation at admission, throughout the ICU stay and at ICU discharge. The global, especially cardiovascular, assessment of each subject will be performed through a complete clinical exam, instrumental tests (electrocardiogram, echocardiogram) and biological parameters. Blood and urine samples will be collected at admission and at discharge with the primary goal to assess effectiveness of routine and novel cardiovascular, inflammatory and renal biomarkers, with potential interest in risk stratification for patients who survive an ICU stay. The follow up will include a careful tracking of patients through telephone calls and questionnaires at 3, 6 and 12 months after ICU discharge. FROG-ICU aims to identify the clinical and biological phenotype of patients with different levels of probability of death in the year after ICU discharge.

**Discussion:**

FROG-ICU has been designed to better understand long term outcome after ICU discharge as well as risk factors for all-cause and cardiovascular morbidity and associated mortality. It is a large prospective multicenter cohort with a biological (on plasma and urine) collection and one-year follow-up of ICU patients. FROG ICU will allow performing a risk stratification of ICU survivors as to recognize the subset of patients who may benefit from an early intervention to allow decreased cardiovascular morbidity and related mortality.

**Trial registration:**

ClinicalTrials.gov NCT01367093.

## Background

Numerous studies have been designed to investigate the early mortality of patients admitted in ICU. They focus on mortality at ICU discharge, at 28 days or/and at hospital discharge [1–3]. Case fatality is high, ranging from 14 to 44 % [1, 4–6] and up to 50 % in septic shock patients [7, 8]. Although many tools are available to assess the severity of illness and help clinicians to determine a prognosis during an ICU stay (Table 1), much less is known about what happens after ICU and hospital discharge.

**Table 1 Tab1:** The severity of disease classification systems (or risk scores) most frequently used to evaluate the severity of ICU patients

Score	Patients	Endpoint	Measure	Reference
Acute Physiolosy and Chronic Health Evaluation (APACHE)	All ICU patients	Hospital mortality	Within 24 h of ICU admission	Knauss WA, 1981, 1985 and 1991[67–69], Zimmerman JE 2006 [70]
Simplified Acute Physiology Score (SAPS)	All ICU patients	28-day mortality	Once, at 24 h after ICU admission	Le Gall JR, 1993 [50] and Moreno RP 2008 [71]
Sequential Organ Failure Assessment (SOFA)	All ICU patients	ICU mortality	Daily	Vincent JL, 1996 [51]
Multiple Organ Dysfunction (MOD) score	All ICU patients	ICU and hospital mortality	Daily	Marshall J, 1995 [72]
McCabe Classification	Infective patients	Hospital mortality	At admission	McCabe WR, 1962 [52]
Sabadell Score	All ICU patients	Hospital mortality	At discharge	Fernandez R, 2006 [73]
Glasgow Coma Scale (GCS)	Traumatic brain injury	Quantify level of consciousness	Daily	Teasdale GM, 1974 [53]
Confusion Assessment method for the ICU CAM-ICU)	All ICU patients	Identify delirium	Daily	Ely EW, 2001 [54]
Injury Severity Score (ISS)	Trauma patients	Hospital mortality	At admission	Baker SP, 1974
Trauma Score	Trauma patients	Hospital mortality	At admission	Champion HR, 1981
Lung Injury Score (Murray Score)	Lung injured patients	Quantify the severity of lung injury	Daily	Murray JF, 1988

To reduce the mortality rate of ICU survivors, it is important to identify the group of patients who have a higher probability of death in the year following ICU discharge and to recognize the adjustable factors associated with mortality. Few data have been published regarding the long-term outcome of ICU patients, and most importantly, there are no recommendations for the long-term management of these patients, only experts opinion have been published [9, 10]. Some studies have demonstrated that mortality rates among ICU survivors are higher compared to the general population [11–15] and that ICU stay impact on patients’ quality of life [16]. Moreover, other studies [14, 15] found that this over-risk of mortality rates is sustained over time persisting after 5 or 15 years of follow-up. Three studies [11–13] reported a worse survival rate for the ICU patients than that for the age-matched control population in the first year after ICU discharge, they also observed that after 2 to 4 years, the survival curves of the two groups became parallel.

Table 2 describes the 15 largest studies from the last 30 years, investigating the one-year outcome of ICU patients and their associated risk factors [11, 13, 15, 17–28]. Using these 15 studies, the pooled estimate of post-ICU one-year mortality rate was 18.8 % (95 % confidence interval: 15.1 – 22.5 %), and the corresponding overall mortality (ICU + post-ICU one-year mortality) was 33.4 % (95 % CI: 27.0 – 39.9 %). However, only six papers out of fifteen had a prospective and multicenter study design (most were post-hoc analyses of prospectively collected data) [11, 19, 20, 23–25]. As expected older age was always associated with long-term mortality, along with APACHE score at admission (or within the first 24 h of the ICU stay). Other factors associated with long-term mortality were the presence and type of comorbidities and the cause of ICU admission.

**Table 2 Tab2:** The 15 largest studies including consecutive ICU patients, reporting one-year outcome and published in the last 30 years

Name	Country	Study design	Recruitment period	Sample size	Age (years)	Sex (M %)	Severity score	ICU mortality	One-year mortality after ICU discharge	Overall mortality	Factors associated with one-year mortality
Zaren B, 1989 [12]	Sweden	O/P/S	1983	978	53.6	58	N/R	9.6 %	18.7 %	26.5 %	age, AC (cardiac arrest, MOF, neurological or CV disease), chronic condition (DM, CHF, cortisone medication)
Dragsted L, 1989 [13]	Denmark	O/P/S	1979-1983	1308	60	50.6	N/R	18.3 %	29.8 %	42.7 %	Age, gender, medical admission category, cancer
Rochwood K 1993 [14]	Canada	O/P/M	N/R	884	N/R	63.2	18.8 .(APACHE II)	14.4 %	23.5 %	34.5	Age
Niskanen M, 1996 [53]	Finland	O/P/M	1987	12180	57.2	62.9	11.7 (APACHE II)	9.9 %	20 %	27.9 %	Age, gender, emergency admission, APACHE II at admission, cancer, CV dz, RF, GI dz, cardiac arrest
Douglas C, 2002 [15]	USA	O/P/M	Feb 1997 - Mar 1999	538	65.8	56.3	N/R	47.4%^a^	32.5 %	64.5 %	N/R
Keenan SP, 2002 [16]	Canada	O/R/M	Apr 1994- Mar 1996	27103	54.3	57.1	N/R	14.3%^a^	10.9 %^b^	N/R	Age, comorbidity (lymphoma/leukemia, HIV, RF)
Kaarlola A, 2003 [17]	Finland	O/P/S	1995	591	N/R	N/R	N/R	N/R	N/R	36 %	N/R
Wright JC, 2003 [9]	UK	O/R/S	Jul 1985- Jul 1992	2104	53.6	N/R	14 (APACHE II)	20.6	20.2	36.7 %	Age, APACHE II, AC(hematological and neurological dz, septic shock)
Bagshaw SM, 2006 [18]	Canada	O/P/M	May 1999 - May 2002	5693	64.9	62	24.9 (APACHE II)	13.4 %	12.9 %	24.5 %	Age, medical diagnosis at admission, APACHE II score, AKI
Williams TA 2008 [11]	Australia	O/P/S	1987-2002	22298	61	67	11 (APACHE II)	10.7%^a^	5.4 %	15.5 %	Age, comorbidity, AC, new diagnosted cancer
Orwelius L, 2010 [19]	Sweden	O/P/M	Aug 2000- Jun 2004	2586	N/R	N/R	N/R	10.2 %	24 %	31.4 %	N/R
Braun A, 2012 [20]	USA	O/P/M	Nov 1997 - Apr 2009	51815	61.7	58.2	N/R	13%^a^	15.3 %	26.3 %	Low preadmission 25(OH)D level
Meynaar IA, 2012 [21]	Holland	O/R/S	Jan 2004 – Dec 2009	3477	N/R	N/R	N/R	8.2 %	20.1 %	26.7 %	Age, APACHE II, discharge not toward home
Grander W, 2013 [22]	Austria	O/P/S	Jan 2001- Jun 2004	1086	N/R	N/R	N/R	9.3 %	15.7 %^b^	N/R	HR before ICU discharge
Luangasanatip N, 2013 [23]	Thailand	O/R/S	Jan 2004 - Dec 2005	10321	57.6	N/R	N/R	31.5 %	20.7 %	45.7 %	AC (cerebrovascular dz, cancer)
FROG ICU	Europe	O/P/M	From Apr 2011 to Dec 2013	2250 (expected)							

*ICU* intensive care unit, *O* observational, *R* retrospective, *P* prospective, *S* single-center, *M* multi-center, *N/R* not reported, *CPR* cardiopulmonary resuscitation, *AKI* acute kidney injury, *WBCC* white blood cells count, *AC* admission category, *MOF* multi organ failure, *DM* diabetes mellitus, *CHF* chronic heart failure, *dz* disease, *CV* cardiovascular, *RF* respiratory failure, *GI* gastrointestinal, *25(OH)D* 25-idrossicolecalciferolo, *HR* heart rate

^a^Hospital mortality (ICU mortality was not available)

^b^Mortality rate was extrapolated from a Kaplan-Meier curve

The association between some biomarker plasma levels and ICU mortality has been studied previously. Although it has been shown that troponin is frequently elevated in ICU patients (from 42.1 to 47.3 %) [29, 30], only 22.2–25.8 % of those patients meet the diagnostic criteria for myocardial infarction. More importantly, elevated cTn during ICU stay was associated with an increased risk of ICU and hospital mortality (OR 2.53; 95 % CI, 1.89 to 3.38) [31–36]. Natriuretic peptide (NPs) levels were also associated with patients’ outcome. It has been demonstrated that brain natriuretic peptide (BNP) level can predict mortality at 6 months after hospital discharge for patients admitted with acute heart failure [37]. These results have been confirmed by other investigators in heart failure patients admitted to the ICU [38]. High BNP levels are also associated with 30-day mortality in septic shock patients [39, 40]. Similarly, biomarker of inflammation and renal function have been shown to be associated with mid- and long-term outcome [41–47].

Thus, measuring cardiovascular, inflammatory and/or renal biomarkers at ICU discharge could be useful in early recognition of high risk patients in whom potential preventive or curative strategies could improve outcomes. Furthermore measuring biomarkers at discharge may allow risk stratification of patients for whom close clinical monitoring as well as chronic life-saving treatments should be introduced. For instance, implementation of oral beta-blocker at ICU discharge has proven benefits in acute heart failure patients who were admitted to the ICU for inotropic treatment (dobutamine or levosimendan) and who received oral beta-blocker therapy at discharge [48]. This has been confirmed on survival at one year after discharge in ICU patients admitted for acute respiratory failure [49].

Here, we describe the design of the French and euRopean Outcome reGistry in Intensive Care Unit (FROG-ICU), the main objective of which is to assess the incidence and identify the risk factors of mortality during the year following discharge from the ICU. This identification of the risks will be based on the patients’ evaluations throughout their ICU stays, using clinical and “routine” biological parameters (including creatinine, sodium, potassium, hemoglobin, etc.…) as well as ICU severity score systems that are already being used to assess short-term mortality as described in Table 1. In addition, the effectiveness of novel cardiovascular biomarkers, including highly sensitive troponin, natriuretic peptides, sST2 and adrenomedullin (Table 3) to early assess adjustable factors associated with long term mortality will be evaluated.

**Table 3 Tab3:** Cardiovascular, inflammatory and renal biomarkers of potential interest in predicting long-term mortality in critically ill patients

Name	Function	Clinical interest	References
Cardio-vascular biomarkers			
copeptine	Peptide of stress deriving from vasopressine	marker of cardiovascular disease	Khan SQ, 2007
Proenkephalin	endogenous opiod polypeptide hormon	marker of cardiovascular and cerebrovascular disease	Seizinger BR, 1985
Troponin I us	part of troponin complex, heart contraction	marker of myocyte injury	Labugger R, 2000
Troponine T hs	part of troponin complex, heart contraction	marker of myocyte injury	Labugger R, 2000
Brian natriuretic peptide (BNP)	increase of natriuresis and decrease of vasculare resistance	marker of myocyte stress	Davidson NC, 1994
N-terminal pro-BNP (NT-proBNP)	biologically inactive segment of BNP	marker of myocyte stress	Moe GW, 2007
adrenomedullin (ADM)	vasodilatation, induction of angiogenesis, protection against oxydative stress and hypoxic injury	marker of myocyte stress	Khan SQ, 2007
Soluble ST2	involved in cardiac remodeling and fibrosis	marker of myocyte stress	Shah RV, 2010
galectine 3	involved in inflammation, fibrosis and neoplastic transformation	marker of heart failure	de Boer RA, 2009
Biomarkers of infection and/or inflammation			
C-reactive protrine (CRP)	acute-phase protein	marker of inflammation/infection	Elster SK, 1956
Interleukine 6	pro-inflammation and anti-inflammation cytokine	marker of inflammation/infection	Castell JV, 1990
procalcitonin (PCT)	precursor of calcitonin	marker of infection, mostly bacterial	Jones AE, 2007
Renal biomarkers			
Plasmatic cystatin C	protein derived by all nucleated cells, readsorbed by proximal tubular cells	marker of decrease glomerular filtration rate	Roos JF, 2007
Urinary cystatin C	protein derived by all nucleated cells, readsorbed by proximal tubular cells	marker of renal tubular injury	Roos JF, 2007
Plasmatic and urinary neutrophil gelatinase associated lipocain (NGAL)	involve in innate immunity	marker of renal tubular injury	Kjeldsen L 1993

## Methods and Design

### Study design

The French and European Outcome Registry in Intensive Care Units (FROG ICU) study is a prospective, observational, multicenter cohort study, designed to assess the incidence and to identify the risk factors of mortality during the year following discharge from the ICU. The study will be conducted in France and in Belgium in accordance with Good Clinical Practice, Declaration of Helsinki 2002, validated by the ethical committee (Comité de Protection des Personnes - Ile de France IV, IRB n°00003835. Comission d’éthique biomédicale hospitalo-facultaire de l’hôpital de Louvain, IRB n°B403201213352) and was registed on ClinicalTrials.gov (NCT01367093). The study consists of two phases (Fig. 1): initially, all patients admitted to any of the participating centers during the recruitment period will be screened for the eligibility criteria listed below; subsequently, all patients included in the study who survive to ICU discharge will be followed up for one year through a telephone call and postal questionnaires at 3, 6 and 12 months.

**Fig. 1 Fig1:**
[figure not shown]
FROG-ICU study schema

### Participants

The study will involve 28 medical, surgical or mixed ICUs in 19 hospitals. The study cohort will include all consecutive patients who are admitted in ICU to any of the participating centers during the recruitment period when the following inclusion criteria are met: invasive mechanical ventilation support for at least 24 h and/or treatment with a positive inotropic agent (except dopamine) for more than 24 h. Because the ethical committee waived the need for written consent, all patients and/or next of kin will be informed and will orally consent to participate; consent was documented in the medical record by the investigator. Exclusion criteria are the following: less than 18 years old; severe head injury (initial Glasgow Coma Scale < 8) or brain death or a persistent vegetative state; pregnancy or breastfeeding; transplantation in the past 12 months; not expected to survive or to leave the hospital; and/or no social security coverage.

### Duration of the study and number of participating centers

The duration of participation for a patient will be a maximum of 12 months after ICU discharge. The inclusion period for any center is 32 months, and we hypothesize that the average number of patients to be recruited in each center would be 10 per month. The total study duration is 44 months.

### Study objectives

#### Primary objective

The primary purpose of this study is to assess the incidence of all-cause mortality in the year following an ICU stay and to identify the factors associated with mortality; those factors include both the clinical-biological factors and the ICU risk scores.

#### Secondary objectives

The secondary objectives of this study are: 1) to determine the incidence and the risk factors of cardiovascular morbidity and mortality in the year following an ICU stay; 2) to evaluate quality of life in the year following an ICU stay; 3) to assess the role of novel biomarkers in assessing long-term outcome after ICU discharge (Table 3).

### Data collection and biological samples

For each patient included, an electronic case report form will be completed that documents relevant information about the ICU stay and the one-year follow-up period. At the time of inclusion, the following will be collected: demographics, data on past medical history, ICU admitting diagnosis, hemodynamic (non-invasive and invasive) and respiratory parameters, severity of disease classification systems (SAPS-II, SOFA, CAM-ICU, McCabe Classification and GCS) [50–54]; digital electrocardiogram (EKG), recorded with CarTouch (Cardionics S.A., Bruxelles, Belgium), a high-definition electrocardiograph provided with TeleTouch software for the automatic transfer of the EKG to the informatics system. Routine laboratory tests will be performed. In 9 ICUs, an echocardiogram will also be performed within a few hours of inclusion. During the first 3 days of each ICU stay, respiratory and cardiovascular parameters (including hemodynamic and EKG) will be recorded daily and subsequently twice a week; SOFA score will be performed the first 3 days after inclusion, and routine biomarkers will be measured according to physician practice. Renal replacement therapy, death and cause of death in ICU will be collected.

The following data will be collected at ICU discharge: clinical parameters, digital EKG and routine biological assessment, ICU length of stay, duration of mechanical ventilation, SOFA score, treatment and results of echocardiogram at discharge when performed.

All patients included in the study population who survive to ICU discharge will be followed up for one additional year or until death, except for severely disabled subjects (Glasgow Outcome Scale < 4 at discharge). One-year outcome will be evaluated through data collection at 3, 6 and 12 months after ICU discharge. At those time points, patients will be contacted by telephone, and information about vital status (patient dead or alive), re-hospitalization, and cardiovascular morbidity will be recorded. For patients lost of follow-up, the vital status will eventually be checked through the national health services records when available. In addition, 4 follow-up questionnaires will be submitted to the study population: the Hospitalization Anxiety and Depression Scale (HADS) [55] and the Short Form-36 (SF-36) [56, 57] at discharge and at 3, 6, and 12 months after and the Impact of Event Scale-Revised (IES-R) [58] at 3, 6 and 12 months; a social questionnaire for assessing patients’ social environments (actual occupation, resumption of activity, level of income, marital status,…) will be submitted at 3 months after discharge.

A biological collection will be created with blood (3x10 ml in EDTA and aprotinin) and urine (10 ml) samples collected at two different time points: admission and discharge. The biological collection will allow for the measurement of novel biomarkers in a central laboratory. Table 3 lists the biomarkers with potential interest for the risk stratification of patient who survive an ICU stay.

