### Statistical analysis

Primary analysis will be performed on all patients included in the cohort. Only patients who withdrew consent will be excluded. Patients who decided to stop tracking or who were lost to follow-up will be included in the analysis. Any missing value will be replaced by the previous value (the last value carried forward method). Sensitivity analyses for missing values will be conducted, for example, using a multiple imputation (MICE, multiple imputation by chained equations [59]. All tests will be bilateral formulation, with a risk of type I error of 5 %.

Calculating the number of subjects required is based on the primary endpoint, i.e., the impact and the risk factors on one year all-cause mortality. The study of the literature and the completion of the preliminary inquiry (conducted in December 2009) in 14 centers that participated to the study conduct us to assume a 1-year mortality after ICU discharge of 18 %. To ensure detection with a power of 80 % of binary prognostic factors with a prevalence of 33 % and an expected OR of 1.5 and a probability of death of approximately 18 %, 1636 patients should be included in this study [60]. Assuming a rate of refusal and/or follow-up losses of 10 %, the number of patients to be included in the one-year follow-up amounts to 1800. The expected in-ICU mortality rate is 25 %. Thus, taking into account these results, the number of patients to be included is 2250.

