The primary analysis will be based on the research of the determinants of 1-year mortality of patients included in the FROG-ICU (i.e., ICU patients who needed mechanical ventilation for more than 24 h and/or treatment with a positive inotropic agent over 24 and who were discharged alive from the ICU) among clinical and biological variables and biomarkers of common interest (i.e., troponins, natriuretic peptides). The regression model used will be the logistic model. The log-linearity of the quantitative variables will be systematically evaluated, and, if appropriate, variable transformations will be performed. A selection model process will be performed using stepwise selection method. The selection process model will be further validated by bootstrap [61]. The existence of any collinearities will be observed, and a test of goodness of fit will be performed using the test and the van Cessie Houwelingen method [62]. Finally a cross-validation procedure will be performed. The measures of association will be provided, with odds ratios and confidence intervals at 95 %. An estimate of related risks will also be conducted. Finally, the overall incidence of 1-year mortality will be estimated at a confidence interval of 95 %.

As it is now recognized that highlighting the statistically significant association between new biomarkers and patient outcomes is not sufficient to demonstrate the interest of these biomarkers in terms of risk prediction [63–65]. We will use the proposed methodology of Pencina et al., which has been used in multiple articles of application. For each biomarker of interest, the net reclassification improvement (NRI) and integrated discrimination improvement (IDI) will be calculated, and comparisons between different biomarkers will be performed [64].

Regarding quality of life, a strategy similar to that outlined for the 1-year mortality analysis will be used to assess its impact and to highlight the predictors of impaired QoL at 6 months or 1 year. QoL will be estimated using the SF-36 score (ranging from 0 to 100) [66]. Altered QoL is considered when SF-36 is lower than 50. In addition, the value of the SF-36 measured in the FROG ICU study will be compared with the values that are typically found in healthy populations of the same age and sex. Interaction between quality of life and social life will be assessed by using information from the social questionnaire.

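### ICU survivors with severe disability at discharge are exempt from the one-year follow-up, yet the stated analysis set includes them, so their primary outcome is missing by design

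*Protocol article*

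**What the plan says.** Four statements in the protocol article bear on who is followed and who is analysed.

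- **Study design:** "all patients included in the study who survive to ICU discharge will be followed up for one year". No exception is given.
- **Data collection and biological samples:** survivors "will be followed up for one additional year or until death, except for severely disabled subjects (Glasgow Outcome Scale" below 4 at discharge). The same paragraph then lists vital status, rehospitalisation and cardiovascular events by telephone at 3, 6 and 12 months, and after that the questionnaires. Nothing ties the exception to the questionnaires alone. A check of national health records is planned for patients lost to follow-up, where such records exist.
- **Statistical analysis, first paragraph:** "Primary analysis will be performed on all patients included in the cohort", and "Only patients who withdrew consent will be excluded". For gaps in the data: "Any missing value will be replaced by the previous value (the last value carried forward method").
- **Statistical analysis, primary model:** the population is the included patients "who were discharged alive from the ICU", with no mention of disability.

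The exclusion criteria under Participants do not list severe disability at discharge. They do remove some patients who would fall into that category: severe head injury, brain death, persistent vegetative state, and patients judged unlikely to survive or to leave hospital.

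**The concern.** The primary objective is the incidence of all-cause death in the year after an ICU stay and the factors associated with it. The follow-up exception withholds that outcome from a subgroup defined by a marker that plausibly predicts death, while the analysis set still contains the subgroup. The analyst is left with two routes, and the article does not choose between them.

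1. **Drop the group.** This contradicts the rule that only consent withdrawals are excluded. It also changes the target, without saying so, from ICU survivors to less disabled ICU survivors.
2. **Keep the group under the last-value rule.** The last known vital status of these patients is alive at ICU discharge, so read literally they enter the logistic model as one-year survivors.

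The first route leaves the risk model with no information on the most disabled survivors. The second gives it false information, because any deaths among them are recorded as survival. Either way the stated aim of stratifying ICU survivors by risk is weakened for this group. The comparison in Table 2 with earlier studies of consecutive ICU patients is also blurred.

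**Working it through.** **Inputs from the Statistical analysis section.** Expected one-year mortality after ICU discharge 18%; required number 1636, based on 80% power, a two-sided 5% test, factor prevalence 33% and odds ratio 1.5.

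**The plan's own figure.** Take 18% as the risk in patients with the factor. The odds without it are (0.18/0.82)/1.5 = 0.146, a risk of 12.8%. A two-proportion calculation with groups in the ratio 33:67 gives 1652, about 1% above 1636. With 18% as the overall risk the same method gives 1394. Nothing below depends on which reading was meant; 1636 serves only as the yardstick for precision.

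**Yardstick.** 95% half-width at 18% and n = 1636: 1.96 × √(0.18 × 0.82 / 1636) = 1.96 × 0.0095 = 0.0186, or about 1.9 points.

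**Assumptions (not in the article).** s = share of survivors with Glasgow Outcome Scale below 4; m = their one-year mortality; 18% in all other survivors.

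- True mortality = (1 − s) × 0.18 + s × m
- Reported if dropped = 0.18; bias = s × (0.18 − m)
- Reported if scored alive = (1 − s) × 0.18; bias = −s × m

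| s | m | True | Dropped (bias) | Scored alive (bias) |
|---|---|---|---|---|
| 5% | 30% | 18.6% | 18.0% (−0.6) | 17.1% (−1.5) |
| 5% | 40% | 19.1% | 18.0% (−1.1) | 17.1% (−2.0) |
| 10% | 30% | 19.2% | 18.0% (−1.2) | 16.2% (−3.0) |
| 10% | 40% | 20.2% | 18.0% (−2.2) | 16.2% (−4.0) |

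If the group is dropped, one of the four cases exceeds the half-width. If it is scored alive, three of the four do.

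**Wider range.** With s = 5-20% and m = 25-50%, the understatement runs from 0.35 points (0.05 × 0.07) to 6.4 points (0.20 × 0.32) if dropped, and from 1.25 points (0.05 × 0.25) to 10.0 points (0.20 × 0.50) if scored alive.

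**Alternative anchor.** If 18% is instead the mortality of all survivors, as the article words it, the others have (0.18 − s × m)/(1 − s), and the bias from dropping becomes s × (0.18 − m)/(1 − s). For s = 5%, m = 30% this is 0.05 × (−0.12)/0.95 = −0.6 points. For s = 10%, m = 40% it is 0.10 × (−0.22)/0.90 = −2.4 points. The bias from scoring alive stays at −s × m. The choice of anchor changes little.

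**Does another provision cure it?** The records check is written for patients lost to follow-up. A patient exempted from the start is not clearly one of them. Multiple imputation is offered only as a sensitivity analysis ("Sensitivity analyses for missing values will be conducted, for example, using a multiple imputation"). With no observed outcomes in the group, it would extrapolate from less disabled patients.

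**The case against.** The strongest reply is that the clock for the primary endpoint starts at ICU discharge and the Glasgow Outcome Scale is scored at discharge. For this endpoint disability is a baseline characteristic, and restricting on it narrows the target population without biasing estimates inside that population. That is correct for a declared restriction. Here the restriction appears only in the follow-up rule, while the analysis section describes a population that includes the group. What stands is that an openly restricted target would be a coherent alternative.

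It can also be said that the Study design sentence is a summary and the Data collection sentence is the detailed rule. That weakens the first contradiction, but not the one with the Statistical analysis section. The exception may have been meant only for questionnaires that these patients could not complete; the wording does not say so.

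Three points limit the size. The Participants exclusions already remove part of the group, so its share and mortality are uncertain. The larger biases need a high share, high mortality and the carry-forward reading together. The 10% allowance for refusal and follow-up losses might have been meant to absorb these patients; the article does not say, so a sample-size shortfall cannot be charged to this exception.

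Two stronger readings are tempting and are not supported. A reader might infer that these patients will be scored alive. The last-value rule allows that if taken literally, but the patients the section names as retained are those who stop tracking or are lost, not those never scheduled for follow-up. A reader might also infer from the opening sentence of the Statistical analysis section that ICU deaths enter the primary mortality model. The later paragraph limits that model to patients discharged alive.

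**Conclusion.** The follow-up rule and the analysis set conflict, and the conflict affects the primary outcome. As written, one-year vital status is not collected for survivors with Glasgow Outcome Scale below 4 who belong to the stated analysis population, and no other provision clearly recovers it.

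The direction under the dropping route rests on one assumption: that this group's mortality is above that of other survivors. This is reasonable but not documented. Under the scored-alive route, any death in the group lowers the estimate. The size is illustrative only, ranging from less than the sampling error to about twice it (4.0 against 1.9 points) in the main scenarios. The documents do not support a claim that the incidence will be wrong by a particular amount. They do show that the incidence and the risk model would not describe the population the article names. The point should be settled because it concerns the primary question and is cheap to resolve.

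**What to change.** 1. In Data collection and biological samples, limit the exception to the patient-completed questionnaires (SF-36, HADS, IES-R and the social questionnaire).
2. Collect 12-month vital status for every patient discharged alive, and state that the national-records check covers survivors with Glasgow Outcome Scale below 4 as well as those lost to follow-up.
3. In Statistical analysis, state that vital status is not filled by the last-value rule for this group.
4. Where vital status cannot be obtained, name the restricted target population in Study design and in both paragraphs of Statistical analysis that define the population, and report the number exempted.

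The cost is one vital-status check per exempted patient. The records route is already planned but usable only where records are available. The telephone calls are described as calls to patients, so a call answered by someone else on behalf of a severely disabled patient would need to be written in. The patient questionnaires are unaffected.
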